## Abstract

**Introduction::**

Dental caries is the most frequent oral disease worldwide and the main cause of tooth loss in children and young adults. One of the most frequently affected areas is the occlusal surfaces of the first permanent molars (FPM) due to their morphological complexity. At present, several preventive treatments can reduce the incidence of this disease in school populations. In Mexico, the most commonly used technologies are those derived from some presentation of fluoride; on the other hand, research on this topic has been limited.

**Objective::**

To determine the cost-effectiveness of two different methods for preventing the incidence of caries on the FPM of schoolchildren (6–8 years of age) from public primary schools.

**Material and methods::**

This is a randomized experimental design. Participants will be assigned to two treatment groups of 114 each. In the first group, pit and fissure sealants will be applied, whereas the second group will receive a fluoride varnish. The work will be carried out in schoolchildren that attend public elementary schools in the state of Hidalgo, Mexico. The result variable will be the incidence of caries and the total cost of each of the interventions will be calculated in order to calculate the intervention's cost-effectiveness.

**Conclusion::**

This work will allow us to compare the cost-effectiveness of the pit and fissure sealants and the fluoride varnish in order to determine which offers the best results.

## Introduction

1

Dental caries is one of the most frequently encountered oral health problems worldwide. Official figures report that between 60% and 90% of children worldwide suffer from dental caries and that caries occur mainly among the most socioeconomically disadvantaged populations.^[1]^ It affects different spheres of people's lives and has a negative impact on people's quality of life, which is why it is considered a public health problem.^[2]^ Dental caries is a demineralization process of the hard tissues of the tooth, which generates a softening of the surface and subsurface of the enamel that, if it is not stopped, can generate a cavity and even cause the loss of the dental organ.^[3]^ One of the areas most affected by dental caries are the pits and fissures of the occlusal surfaces^[4,5]^; according to some researchers, these pits and fissures account for about 90% of all caries cases due to the presence of deep and narrow pits and fissures.^[6,7]^ Several studies indicate that occlusal surfaces are more susceptible to decay than smooth surfaces due to a lack of post-eruptive maturation and reduced mineral content.^[6–8]^

Concepts on the management of carious lesions have changed during the last few decades.^[9–11]^ Increasing knowledge about the importance of preventive dentistry and the management of incipient lesions has modified the dentist's typical protocols, specifically by promoting the current focus on less invasive treatments and trying to preserve the greatest amount of enamel for as long as possible.^[9–11]^ Topical fluorides, in their different forms (dentifrices, mouth rinses, gels, and varnishes), allow a local protective effect to be generated on the tooth surface by increasing the exposure time between the fluoride and tooth enamel.^[12,13]^ This increased exposure helps facilitate the remineralization process, which decreases the appearance of new carious lesions in the areas where it is applied. The use of fluorides contributes significantly to the prevention and management of carious lesions.^[12]^ Also, the evolution of dental materials enabled the improvement of preventive methods in dentistry, e.g., the changes in and new types of resins and their application, from the technique of acid etching introduced by Buonocore in 1955 and the development of acrylic resins by Bowen in 1953 to the materials that we know today.

The pit and fissure sealer (PFS) is a low-viscosity resin that penetrates deep pits and fissures. This preventive method reduces the risk that the pits and fissures of the occlusal surfaces become carious by generating a physical barrier that prevents the accumulation of biofilms within these areas.^[14]^ The PFS has been modified over time, resulting in improved retention to the dental surface and decreased working time, which facilitated PFS's application along with the change in coloration offered by some brands. Additionally, some of these products even have technology that allows them to release fluoride, thereby improving the resin's cariostatic actions.^[15]^

In Mexico, dental caries is a public health problem in schoolchildren^[16–25]^; however, the use of preventive methods other than fluoride in school populations has not been studied in terms of the costs involved in its use nor its results in terms of caries reduction.^[26]^ Almost no clinical trials have been published in this country on this topic, which opens up new research avenues that will, eventually, allow health planners to make decisions based on evidence. The objective of this work will be to determine the cost-effectiveness of two different preventive methods in decreasing the incidence of dental caries on the first permanent molars (FPM) of schoolchildren (from 6 to 8 years of age) from public primary schools.

## Methodology

2

### Study design

2.1

This is a randomized experimental design that will be carried out on the FPMs of schoolchildren from public elementary schools in the state of Hidalgo, Mexico. Start date: 2019–03-05.

Hidalgo is one of the 31 states, which, with Mexico City, comprise the 32 Federal Entities of Mexico. It is divided in 84 municipalities and its capital city is *Pachuca de Soto*. Hidalgo is one of the Mexican states that participated in the fluoridated domestic salt program implemented nationally in 1991. Mexico has no water fluoridation program at the national level; however, some states, including parts of Hidalgo, have water with naturally high levels of fluoride. This is not the case in Pachuca, the capital city of Hidalgo.^[27,28]^

### Participants

2.2

The treatments will be carried out within selected public primary schools in selected municipalities of the state of Hidalgo with little access to oral health programs. Participants will be children between 6 and 8 years of age with at least one permanent molar that is healthy and fully erupted with high or moderate risk of caries according to the Scottish Intercollegiate Guidelines Network (SIGN).^[29]^

### Selection criteria

2.3

To be considered to participate in the trial, each potential participant must meet the established inclusion and exclusion criteria. Some of the criteria require oral examination within the baseline measurement, which, may result in some children not participating in the intervention and, therefore, the study.

### Inclusion criteria

2.4

Children must be from 6 to 8 years of age, belong to the selected public elementary schools, and:

Have at least one first molar that is healthy and fully erupted;Whose parents sign the informed consent form; andDecide to participate in the intervention.

### Elimination criteria

2.5

Fixed orthodontic appliances;Disability;Systemic disease; orAny alteration of the oral cavity.

### Trial intervention

2.6

The PFSs to be used in this study have been used for years in other populations. Children will be randomly assigned to either the PFS or varnish group and each subject will remain in their assigned group throughout the study.

#### Pit and fissure sealant

2.6.1

The PFS that will be used for this study is Clinpro3M. This PFS changes color when being light-cured and has a low viscosity, which allows it to have excellent penetration inside the pits and fissures. It has fluoride release capability and is applied through the total enamel etching system.

The application of the sealant will be carried out within the public primary schools with the help of a portable tripod and using natural light. Sealers will be reviewed every 3 months for a period of 24 months. In cases of partial or total release, the sealant will be reapplied.

#### Fluoride varnish

2.6.2

The varnish used in this study will be DuraphatColgate, which consists of a 5% fluoride varnish containing 22,600 ppm of fluoride suspended in a resin base. It is an easy product to apply since it adheres quickly in the presence of saliva and its color allows good visual control.

Once the baseline measurement is obtained, the application will be made within the selected schools with prior prophylaxis and during the first hour of classes to ensure that the children do not consume food until at least 2 h after the treatment, considering the time of the meal recess.

The revisions and reapplications will occur every 3 months during the follow-up period of 24 months.

### Risks and adverse effects

2.7

The procedures used in this intervention are currently used as standard treatments for clinical care. The risks for the participants are minimal and basically the same as those of patients that are exposed to these procedures during routine clinical care. Although there are very few reported cases of allergies or hypersensitivity to these products, it will be necessary to question the parents about possible reactions to some of the compounds of the Duraphat varnish or the Clinpro sealer.^[29–32]^ Adverse events and other unintended effects of trial interventions will be reported to the committee of the university where the protocol was approved. The study will be audited every 6 months, and will be carried out by the IRB.

### Measuring the effectiveness of the intervention

2.8

The primary results for this project are the incidence of caries at 6, 12, 18, and 24 months between the sealant and varnish groups.

The incidence of dental caries considers the measurement of the existence (or not) of visible changes in the surface of the enamel compared to the basal measurement. In the clinical evaluation, visual caries detection and a standardized and international caries measurement system, known as International Caries Detection and Measurement System (ICDAS), will be used.

The reviews will occur every 6 months for a 24-month period.

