### Sample size

2.10

The sample size was calculated using a formula for the difference of proportions. The proportions used in this calculation were the decreases in incidence reported with the use of fluoride varnish (60%) and PFS (40%), a power of 80%, and an α of 95%, which gave a sample size of 97 subjects. In the end, 15% more subjects were added due to the losses to follow-up reported in longitudinal studies, which amounted to 114 subjects for each group.

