#### Collection and analysis of the data regarding caries incidence

2.14.1

The incidence of dental caries will be analyzed using the ICDAS at 6, 12, 18, and 24 months after the intervention. The data will be collected by a researcher trained in this measurement system.^[34,35]^ The collected data will be captured according to the codes established in the ICDAS manual.

Caries status

0 = Sound

1 = First visual change in enamel (whitespot seen after 5 s air drying).

2 = Distinct visual change in enamel (whitespot seen without air drying).

3 = Localized enamel breakdown due to caries with no visible dentin

4 = Non-cavitated surface with underlying dark shadow from dentin

5 = Distinct cavity with visible dentin

6 = Extensive distinct cavity with visible dentin. An extensive cavity involves at least half of a tooth surface and possibly reaching the pulp.

7 = Tooth extracted because of caries (tooth surfaces will be coded 97)

8 = Tooth extracted for reasons other than caries (tooth surfaces will be coded 98)

9 = Unerupted (tooth surfaces coded 99)

In each of the measurements, the change occurred in the occlusal surfaces of the first permanent molars between the two preventive treatments used to determine which is more effective in preventing caries in each of the established periods.

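### Caries incidence at four visits is primary with none ranked, while the sample size allows for a single comparison at two-sided 5%

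*Protocol article*

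**What the plan says.** Section 2.8 defines the primary result of the trial: "The primary results for this project are the incidence of caries at 6, 12, 18, and 24 months between the sealant and varnish groups". The outcome is binary and refers back to baseline, being "the measurement of the existence (or not) of visible changes in the surface of the enamel compared to the basal measurement".

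Section 2.14.1 repeats the four analysis times ("The incidence of dental caries will be analyzed using the ICDAS at 6, 12, 18, and 24 months after the intervention"). It gives the purpose of the comparison at these visits as "to determine which is more effective in preventing caries in each of the established periods".

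Section 2.10 uses a formula for a difference between two proportions, 60% and 40%, with 80% power and "an α of 95%, which gave a sample size of 97 subjects". The allowance for attrition follows: "15% more subjects were added due to the losses to follow-up reported in longitudinal studies, which amounted to 114 subjects for each group". That section names no time point and mentions only one comparison.

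On costs, section 2.9 estimates them for the same evaluation periods, and section 2.14.2 speaks of cost-effectiveness ratios in the plural. Neither says which period supplies the main ratio.

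The article gives no ranking of the visits, no adjusted significance level, no requirement that all visits agree and no single test across visits.

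**The concern.** A trial with one primary comparison at 5% carries a 5% risk of declaring a difference that does not exist. Here four comparisons hold primary status and each is meant to show which treatment is better. If success at any one of them supports the claim of superiority, the risk is that of the four taken together, which is larger than 5%.

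The sample size makes no provision for this. An adjustment added later in an analysis plan would control the error but would cost power, because the number of children was set for one test at the full level.

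Leaving all four visits equal also leaves open which one carries the headline result, for caries and for cost-effectiveness. That choice could then be made after the data are seen.

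**Working it through.** **1. Reproduce the stated sample size.** Inputs from section 2.10: proportions 0.60 and 0.40, power 80%. The level printed there is the confidence level, so I read it as a 5% error. Sidedness is not stated. With a pooled variance under the null and p̄ = 0.50:

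n = [1.960·√(2·0.50·0.50) + 0.842·√(0.60·0.40 + 0.40·0.60)]² / 0.20²
= [1.386 + 0.583]² / 0.04 = 96.9, so 97 per group.

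This is an exact match at two-sided 5%. A one-sided 5% test gives 77, and a two-sided continuity-corrected test gives 107. Allowance for losses: 97 / (1 − 0.15) = 114.1, which gives the stated 114. The figures are therefore those of one comparison at two-sided 5%.

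**2. Upper benchmark.** Four independent tests at 5%: 1 − 0.95⁴ = 0.185.

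**3. Allow for correlation.** Cumulative results at successive visits share children and events, so the four tests are positively correlated. For cumulative incidences p₁ < p₂ at two visits with no treatment difference, the test statistics have correlation √[p₁(1 − p₂) / (p₂(1 − p₁))]. The article gives no expected incidence or accrual pattern, so these are assumptions and a range is shown. Each visit is tested at two-sided 5%.

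| Assumption (no true difference) | Chance of at least one significant visit |
|---|---|
| Equal information increments, normal approximation | 12.6% |
| Steady accrual, 24-month incidence 10% to 60%, normal approximation | 12.7% to 14.3% |
| Simulation, 97 per arm, constant hazard, uncorrected test, incidence 20% / 30% / 50% | 12.6% / 13.3% / 13.4% |
| Simulation, 97 or 114 per arm, linear accrual, uncorrected test, incidence 30% or 50% | 13.5% to 14.2% |
| Most caries early (35%, 42%, 46%, 50% at the four visits), normal approximation | 10.2% |
| Most caries late (2%, 8%, 20%, 50%), normal approximation | 16.4% |
| Simulation, 97 per arm, constant hazard, continuity-corrected test, incidence 20% / 30% / 50% | 7.2% / 8.2% / 9.2% |
| Independent tests | 18.5% |

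The continuity-corrected test gives lower figures because at these sizes it rejects in only about 2% to 4% of trials at each visit. Even so, the four together exceed 5%.

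**4. What keeping all four visits primary would require.** With Bonferroni, each test is at 0.05 / 4 = 0.0125, with critical value 2.498:

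n = [2.498·0.7071 + 0.583]² / 0.04 = 138 per group.

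Allowing for 15% loss, 138 / 0.85 = 162.4, so 163. With 97 evaluable per group, power for each comparison falls from 80% to about 62%. Using the correlation between visits gives a milder nominal level of about 0.016 to 0.018 per test under steady accrual, still well below 5%.

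**The case against.** Several points on the other side carry weight.

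- **The 13% is conditional.** The article states no significance level per visit. Section 2.14 says only that non-parametric tests will be used, so the exact test is open. The figure moves with the test and with how caries accrue. This stands, and for that reason a range is given. The direction does not change: every case tried exceeds 5%.
- **No any-visit rule is written.** Section 2.14.1 can be read as four period-specific statements, and its sentence is grammatically incomplete. This also stands: the inflated error applies if any one significant visit is taken as showing superiority. Nothing in the text rules that use out.
- **Adjustment belongs in an analysis plan.** An article may leave it there, and its absence is not the point. The point is what the article does fix: four unranked primary results, a conclusion sought in each period, and a size for one comparison.

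Two stronger readings are tempting but not supported. A reader might infer that the visit results will contradict one another because early enamel changes can remineralise. The introduction describes fluoride as reducing the appearance of new lesions. It does not say that recorded lesions return to sound, and no figure supports such conflict. That reading also sits badly with the cumulative incidence on which the 13% rests. A reader might also infer that the effect for the cost-effectiveness ratio is wholly undetermined. Section 2.9 matches costs to the same evaluation periods, so period-specific ratios can be formed. Only a designated main period is lacking.

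**Conclusion.** The concern holds in a conditional form. The primary outcome in section 2.8 and the period-by-period conclusion in section 2.14.1 do not fit a sample size for one comparison at two-sided 5%. Treating any significant visit as proof of superiority would give a false-claim risk of about 13%. That figure assumes cumulative incidence, steady accrual, an uncorrected test and 5% at each visit. A fair range is 7% to 16%, and independent tests would give 18.5%. The risk would stay at or below 5% if one visit were designated primary or if significance were required at all four, but the article says neither. The trial remains sound in design. What needs settling is which result carries the claim.

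**What to change.** In section 2.8, name cumulative caries incidence from baseline to 24 months as the single primary outcome, tested at two-sided 5%. State there that it is the effect used in the main cost-effectiveness ratio. In section 2.14.1, report 6, 12 and 18 months as secondary estimates with confidence intervals, and treat their period-specific cost-effectiveness ratios as secondary too.

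This costs a few sentences and no additional data, visits or children. The stated 97 (114 with losses) per group then matches the analysis. The small downside is that no confirmatory claim can be made at the earlier visits. If such claims matter to the investigators, a fixed testing order starting at 24 months, an adjusted level or one test across visits would also control the error. A Bonferroni adjustment would need about 138 per group (163 with losses).

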#### International caries detection and measurement system (ICDAS)

2.8.1

ICDAS is a caries measurement system that uses the visual method to detect caries. It can measure carious lesions at the subclinical stage; ICDAS considers coloration changes sufficient to identify lesions in the incipient stages and does not recommend the use of explorers.

This measurement system examines five surfaces and uses codes that range from 0 to 6, depending on the severity of the injury, where 0 indicates a healthy surface.^[33–35]^ This system also evaluates the condition of the surface in terms of restorations, where it uses codes that range from 0 to 8, depending on the type of restoration used.^[33–35]^ For this study, the examiners will be calibrated and previously standardized (Kappa > 0.80).

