### Blinding and masking

2.13

In this study, the type of blinding that will be applied will be simple since the participants will not know what type of technology will be used in each individual. To guarantee this, the subjects will not observe the applications that the other participants will receive. This implies that the subjects will pass individually and be isolated from the other subjects during their participation. In addition, a very similar protocol will be carried out for the application, such as prophylaxis, and therefore the participant will not know what type of treatment will be applied.

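### The primary event counts any visible enamel change, but resin covers the scored pits and fissures in one arm only, so early lesions are likely to be under-detected with sealant

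*Protocol article*

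**What the plan says.** **Event.** Section 2.8 of the protocol article states: "The primary results for this project are the incidence of caries at 6, 12, 18, and 24 months between the sealant and varnish groups". The event is defined there as "the measurement of the existence (or not) of visible changes in the surface of the enamel compared to the basal measurement". No minimum ICDAS code is named.

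**How it is read.** Section 2.8.1 makes detection visual: "ICDAS considers coloration changes sufficient to identify lesions in the incipient stages and does not recommend the use of explorers". Section 2.14.1 lists the codes. The lowest lesion code is "1 = First visual change in enamel (whitespot seen after 5 s air drying"; code 2 is a white spot visible without drying. Code 3 is the first with enamel breakdown.

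**Where it is read.** Section 2.14.1 compares "the change occurred in the occlusal surfaces of the first permanent molars between the two preventive treatments".

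**What lies on that surface.** The Introduction describes the sealant as a low-viscosity resin that enters pits and fissures and forms a physical barrier there. Section 2.6.1 says "This PFS changes color when being light-cured and has a low viscosity". It also has sealants checked every 3 months for 24 months and replaced after partial or total loss. The varnish arm (section 2.6.2) has no such covering.

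**Who is blinded.** Section 2.13 says "the type of blinding that will be applied will be simple since the participants will not know" which treatment is used. Section 2.14.1 has a trained researcher collect the outcome data and mentions no masking.

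**The concern.** The outcome is a visual reading of enamel. In one arm, the part of the surface where occlusal caries mostly starts is deliberately kept under resin through all four primary readings; in the other it is exposed. A threshold at the first visible change rests on the faintest signs, which are the ones a resin layer is most likely to obscure. If they are obscured, two equally effective treatments would show a lower incidence with sealant.

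Retained sealant would also tell the examiner the arm, and codes 1 and 2 leave most room for judgement. Calibration to kappa above 0.80 (section 2.8.1) secures agreement between examiners but does not make covered enamel visible. A larger sample would only make a false difference more certain. Sections 2.9 and 2.14.2 build the cost-effectiveness ratios on the same incidence, so any bias passes straight into the trial's main objective.

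**Working it through.** **1. The plan's own figure.** Section 2.10 gives 60% and 40%, power 80%, and what is evidently a 0.05 two-sided test. With the pooled two-proportion formula:

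n = [1.960 × √(2 × 0.5 × 0.5) + 0.842 × √(0.6 × 0.4 + 0.4 × 0.6)]² / 0.20² = 96.9, so 97 per group.

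Allowing for 15% loss, 97 / 0.85 = 114.1, which matches the stated 114. The sample size is not in dispute; 97 per arm is used below as the number followed up.

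**2. Does the argument need an opaque sealant?** Not entirely. The article does not give the opacity of the cured resin. But code 1 requires enamel to be dried for 5 seconds, and enamel under retained resin cannot be dried. At least that code is affected whatever the resin's colour.

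**3. How large could it be?** Assume the same true incidence p in both arms. Let e be the share of events at codes 1 and 2, and h the fraction of those hidden under sealant. Then:

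- observed varnish incidence = p
- observed sealant incidence = p × (1 − e × h)

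The chance of p < 0.05 comes from the two-sided pooled test with 97 per arm. Neither e nor h is in the documents; both are assumptions.

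| p | e | h | Sealant reading | Spurious difference | Chance of p < 0.05 |
|---|---|---|---|---|---|
| 40% | 0.5 | 0 | 40% | 0 points | 5% |
| 40% | 0.5 | 0.25 | 35% | 5 points | 11% |
| 40% | 0.5 | 0.50 | 30% | 10 points | 31% |
| 40% | 0.5 | 0.80 | 24% | 16 points | 67% |
| 30% | 0.5 | 0.20 | 27% | 3 points | 7% |
| 30% | 0.5 | 0.80 | 18% | 12 points | 50% |
| 60% | 0.5 | 0.25 | 52.5% | 7.5 points | 18% |
| 60% | 0.5 | 0.50 | 45% | 15 points | 55% |

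The 67% row, worked through: the difference is 0.16. The pooled standard error is √(2 × 0.32 × 0.68 / 97) = 0.0670 and the unpooled one is √((0.40 × 0.60 + 0.24 × 0.76) / 97) = 0.0660. Then Φ((0.16 − 1.960 × 0.0670) / 0.0660) = Φ(0.44) = 0.67.

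**4. Against the planned difference.** The design looks for 20 points. At a true 60%, missing one third of sealant-arm events (0.20 / 0.60) produces all of it with no real effect; at a true 40%, missing half (0.20 / 0.40) does.

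**The case against.** Five points can be made against this.

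- **Concealment is not documented.** Section 2.6.1 says only that the sealant changes colour on curing, and nothing gives its opacity. A reader might infer that early lesions can be seen almost only in the varnish arm, or that every white spot under resin is lost. The documents do not support that. The sealant sits in pits and fissures, so adjoining occlusal enamel stays visible, and at mild concealment the false-positive chance is only 7% to 11%. This stands, and it limits what can be said about size.
- **Examiner unblinding is inferred.** Section 2.13 does not mention the examiner. Nothing says that the examiner applies treatment, holds the allocation list or scores after reapplication. That is fair. But masking is claimed for participants only, and retained sealant would be seen in any case.
- **The scoring of sealed surfaces may be set elsewhere.** Section 2.8.1 mentions a second set of codes for the restored condition of a surface, and section 2.14.1 refers to the ICDAS manual. The absence of such a rule from a condensed article is therefore not held against the plan. The event definition in section 2.8 is stated outright, however, and a scoring rule cannot recover lesions that were not visible.
- **Early detection is a legitimate aim.** The Introduction stresses managing incipient lesions, and a cut-off at code 3 gives some of that up. This stands as a trade-off.
- **Code 3 is not a clean cure.** Enamel breakdown and underlying shadow (codes 3 and 4) can also lie under resin. The difference is reduced, perhaps not removed.

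**Conclusion.** The concern holds as a likely detection bias of known direction and unknown size. As written, the plan counts the faintest visible enamel change on surfaces that are kept covered in one arm only, and claims no blinding beyond participants. The expected direction favours sealant, in incidence and in the cost-effectiveness ratio.

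With equal true incidence of 40%, 97 per arm and half of events at codes 1 and 2, the chance of a false significant difference runs from 11% (a quarter of those lesions hidden) through 31% (half) to 67% (80%). This rests on the assumed shares. The higher figures should not be read as an estimate for this trial, and the documents do not show that the bias would decide its result. They also give no means of ruling that out.

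**What to change.** **Sections 2.8 and 2.14.1.** Prespecify the between-arm comparison, and the cost-effectiveness ratio, for ICDAS code 3 or worse, a caries-related restoration, or extraction for caries, on first molars sound at baseline. Either:

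- make this the primary event and restate the power in section 2.10; or
- keep the present event and make this a key sensitivity analysis that must agree before one method is called more effective, saying in advance what counts as agreement.

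State that codes 1 and 2 cannot be compared fairly between sealed and unsealed surfaces, and that the code 3 threshold reduces the difference but may not remove it.

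**Section 2.13.** State that examiners cannot be fully masked because sealant is visible. Have an existing staff member who did not apply the treatment do the scoring, without the allocation list and before any reapplication at that visit.

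**Cost.** The codes are already recorded, so no new data are needed, only wording and some rostering of existing staff. The real price is power. As an illustration, read the 60% and 40% in section 2.10 as event rates and suppose half of events in each arm are codes 1 and 2. The comparison becomes 30% against 20%. With 97 per arm, power is Φ((0.10 − 1.960 × √(2 × 0.25 × 0.75 / 97)) / √((0.30 × 0.70 + 0.20 × 0.80) / 97)) = Φ(−0.35), about 36%. The choice between the two options should be made with that calculation done on the sponsor's own expected code 3 rates.
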